### Training curriculum

The sequential learning group (group 1) learn the psychomotor aspects of laparoscopic suturing and knot tying first on the transparent shoebox without having to adjust to the visuospatial orientation inherent to the laparoscopic view of a box trainer. Once they reach the predefined proficiency criteria explained below (Tables 1, 2 and 3), these students then train on the box trainer with laparoscopic view until proficient (Fig. 2). The control group (group 2) learn the psychomotor skills and visuospatial aspects of laparoscopy simultaneously, as is traditionally done. They train using the box trainer with laparoscopic view until proficient in the predefined criteria. Specially trained peer tutors assist trainees during the course of the study and are available on demand in the training room for both groups; this has proven to be beneficial to trainee learning [19].

**Table 1 Tab1:** Procedural proficiency checklist

Procedure assessment			Yes/No
Needle position 1	1	Held at one half to two thirds distance from the tip	
	2	Angle 90° ± 20°	
	3	Uses tissue or other instrument for stability	
	4	Attempts at positioning (≤3)	
Needle driving 1 (entry to incision)	5	Entry at 60° to 90° to the tissue plane	
	6	Driving with one movement	
	7	Single point of entry through the tissue	
	8	Removes the needle along its curve	
Needle position 2	9	Held at one half to two thirds distance from the tip	
	10	Angle 90° ± 20°	
	11	Uses tissue or other instrument for stability	
	12	Attempts at positioning (≤3)	
Needle driving 2 (incision to exit)	13	Driving with one movement	
	14	Removes the needle along its curve	
Pulling the suture	15	Needle on needle holder in view at all times	
	16	Uses the pulley concept	
Technique of knots	17	Correct C-loop (no S- or O-loops)	
	18	Smoothly executed throw, no fumbles	
	19	Correct inverse C-loop (no S- or O-loops)	
	20	Smoothly executed throw, no fumbles	
	21	Knot squared (capsized/reef/surgical)	
	22	Correct third C-loop (no S- or O-loops)	
	23	Smoothly executed throw, no fumbles	
Total points

**Table 2 Tab2:** Knot quality checklist

Knot quality assessment	Available points
No visible gaps between stacked throws	1
Knot tight at base	1
Only edges are opposed (no extra tissue in knot, e.g., back wall)	1
Knot holds under tension	2
Maximum	5

**Table 3 Tab3:** Competency checklist

Competency assessment	Goal	Yes/No
Time (min:sec)	≤01:15	
Procedure	≥18	
Knot quality	≥4	
Accuracy (mm)	≤2	
Competency (if all “Yes” above)

**Fig. 2 Fig2:**
[figure not shown]
Transparent shoebox used by intervention group (left). Box trainer with laparoscopic view used by both groups (right)

Following randomization, participants are put into training pairs, which is a common practice within surgical training [20, 21]. This allows the trainees to give each other real-time competency assessment and feedback, which is motivational [22, 23], in addition to saving time for the trainers, and space in the training center. We recently explored the difference between laparoscopic training alone and in pairs and found there to be no distinction in outcome between the two groups (protocol, own data, unpublished). It has been shown that students – whether alone or in a collaborative pair – can learn as much by observing their peers learn a task as they can by performing the task themselves [24, 25]. This is known as vicarious learning, which typically does not provide for communication between the student being tutored and the student watching. It should be made clear that students in our training environment can communicate directly with one another, which may prove even more useful. Based on these grounds, we believe that the pragmatic aspect of saving time and resources in a busy training center outweighs the potentially confounding effect of partner training.

The student who is watching records the time taken for each attempt of the operating partner, starting from when the needle is grasped and ending once the final knot is tied. All attempts must be completed and the time per attempt must be recorded for each trainee. In the event of technical or instrument failure, e.g., the suture thread getting stuck in the grooves of the instrument, time is stopped and recorded, and “N/A” and a brief description of what happened are written next to the attempt. Rather than mass practice, we implement the more effective interval training [26–28]; trainees are required to switch positions at least every five completed knot attempts. Students train using two laparoscopic needle holders (KARL STORZ GmbH & Co. KG, Tuttlingen, Germany) and a standardized silicone suture pad with diagonal incisions and predefined suture entry and exit points (Fig. 3) (Big Bite Medical GmbH, Heidelberg). The suture material is a Polysorb 3-0 braided absorbable suture with a CV-23 taper ½ 17-mm needle (Covidien^TM^, Minneapolis, MN, USA).

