### Statistical analysis

The empirical distributions of all parameters of interest are described using mean and standard deviation in case of continuous data, with absolute and relative frequencies in case of categorical parameters. Possible difference in the primary outcome, time to reach proficiency, will be tested using a two-sided *t* test. All secondary parameters including subgroup analyses will be descriptively analyzed according to their underlying distribution, two-sided Mann-Whitney *U* tests in case of continuous parameters, and Chi-square test in case of categorical data. Graphical statistical methods will illustrate the findings, whenever appropriate.

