### Sample size determination

Sample size calculation was done with respect to the primary endpoint. A previously evaluated pilot study showed the following data for total training time needed to reach proficiency: mean difference between group 1 and group 2 was 15 seconds; standard deviation in group 1 was 15.6 seconds, whereas it was 22.2 seconds in group 2. This difference can be detected with a two-sided significance level *α* = 0.05 and a power of 1 − *β* = 0.8, with a group size of 27 participants randomized to each group.

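### Students train, time and rate each other in pairs, but the primary t test and the sample size treat all 54 as independent, so 5% error and 80% power are not assured.

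*Protocol article*

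**What the plan says.** Under Randomization, individual students are allocated 1:1 to the two groups. Pairing comes afterwards, under Training curriculum: "Following randomization, participants are put into training pairs, which is a common practice within surgical training". That section describes a close working relationship. Partners talk to each other and give feedback in real time. The one who watches clocks each attempt of the one who operates, and they swap places at least every five completed knots. They rate each other throughout, and the tutor's assessment is requested only once the partner judges the student competent.

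The article accepts pairing on pragmatic grounds. It cites the group's own unpublished comparison of training alone with training in pairs, which "found there to be no distinction in outcome between the two groups". It also concedes, under Randomization and Training curriculum, that a partner may influence outcome, and it plans an exploratory comparison by pair composition.

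None of this reaches the primary analysis. Under Statistical analysis: "Possible difference in the primary outcome, time to reach proficiency, will be tested using a two-sided" t test, with no term for pair. Under Sample size determination, the inputs are a difference, two standard deviations, a significance level and a power, "with a group size of 27 participants randomized to each group". The abbreviation list includes the intraclass correlation coefficient, but the text gives no value for it.

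**The concern.** The two-sample t test and its sample size formula assume that each student's time is independent of every other student's in the same arm. The training design gives reasons to doubt this. Partners share feedback, watch each other's practice and depend on each other's judgement before they can be assessed. A helpful partner or a productive pair can shorten both times, and a poor one can lengthen both.

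If partners' times are positively correlated, 27 students carry less information about the arm mean than 27 independent students would. The t test's standard error is then too small, its p value and confidence interval overstate the evidence, and a correctly analysed trial has less power than stated. This affects the only test that the sample size was built for, in a small trial whose Discussion expects that the result could change training practice.

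**Working it through.** **Inputs from Sample size determination.** Difference 15 ("mean difference between group 1 and group 2 was 15 seconds"), SDs 15.6 and 22.2, two-sided α 0.05, power 0.8, 27 per group. The unit cancels, because only the ratio of difference to SD matters.

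**Assumptions.** Pairs lie within one arm (cluster size m = 2). The within-pair ICC is not given, so values of 0.1, 0.2 and 0.3 are shown.

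**Step 1: reproduce the plan's figure under independence.**
- Common SD = √((15.6² + 22.2²)/2) = 19.19.
- Noncentrality = 15 / (19.19 × √(2/27)) = 2.87.
- With 52 degrees of freedom (df), power is 80.5% at 27 per group and 78.9% at 26. So 27 is the smallest group size that reaches 80%, and the plan's figure is correct for independent students.

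**Step 2: design effect.** DE = 1 + (m − 1) × ICC = 1 + ICC. The effective size per arm is 27/DE.

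**Step 3: true error of the planned t test.** Its standard error is too small by a factor √DE, so the true two-sided error is about 2 × (1 − Φ(1.96/√DE)).

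**Step 4: power of an analysis that respects pairs.** The noncentrality becomes 2.87/√DE. With 27 students per arm there are about 27 pairs in total, hence 27 − 2 = 25 df.

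| Assumed ICC | DE | Effective n per arm | 1.96/√DE | True error of planned test | Noncentrality | Power, pair-respecting |
|---|---|---|---|---|---|---|
| 0.1 | 1.1 | 24.5 | 1.87 | 6.2% | 2.74 | 74.9% |
| 0.2 | 1.2 | 22.5 | 1.79 | 7.4% | 2.62 | 71.2% |
| 0.3 | 1.3 | 20.8 | 1.72 | 8.6% | 2.52 | 67.8% |

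At ICC 0 the planned test keeps its 5% error and 80.5% power. A pair-level test with 25 df would then have 78.8%, so about 1.6 points of the loss in the last column come from degrees of freedom and the rest from correlation.

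**Step 5: check by simulation.** 100,000 trials per setting, 13 pairs plus one single student per arm, SDs as above.
- Planned t test, error at ICC 0 / 0.1 / 0.2 / 0.3: 5.0% / 6.1% / 7.3% / 8.6%.
- Planned t test, rejection rate at a true difference of 15: 80.6% / 79.4% / 78.8% / 77.8%.
- t test on pair means, error: between 5.0% and 5.2% throughout.
- t test on pair means, power at ICC 0.1 / 0.2 / 0.3: 74.2% / 71.2% / 67.7%.

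**Step 6: size needed for 80%.** Applying DE to the plan's own calculation (2n − 2 df) gives 30, 32 and 35 per arm for ICC 0.1, 0.2 and 0.3. Using pair-level df (n − 2) adds one student to each: 31, 33 and 36.

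**The case against.** The strongest counter-argument is that the consequence depends on a quantity the article does not contain. With an ICC of zero nothing changes. With a negative ICC the test is conservative: at −0.2, DE = 0.8, 1.96/√0.8 = 2.19, and the error is about 3%. A negative value is conceivable, for example if watching a slow partner's many attempts shortens one's own training. Each student's time is clocked on that student's own attempts, and proficiency needs a repeat under a trained tutor, which limits what a lenient or strict partner can do. With clusters of two, DE cannot exceed 2. The planned test's rejection rate at the design difference also barely falls. All of this stands, and it bounds the point.

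A reader might therefore infer that the 5% and 80% are wrong. The documents do not support that: they show that independence is assumed without support, not that it fails by a known amount.

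Within-arm pairing is likewise inferred, from pairing after randomisation and the arm-specific curricula. Positively correlated pairs across arms would make the t test conservative instead.

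A reader might also infer from the odd 27 that one student per arm has no partner. The arithmetic is right for within-arm pairs, but how such a student trains is a logistical detail that a condensed article may leave to the full protocol.

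Two possible defences do not stand. The comparison of solo with paired training concerns outcome under the two formats and says nothing on whether two partners resemble each other. The exploratory comparison by pair composition does not correct the primary test. Nor is this detail left to another document, since the article itself states both the test and the sample size.

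**Conclusion.** The point holds in a conditional form and should be fixed. The plan trains students in interacting pairs but tests and sizes the trial as if all were independent. With positive within-pair correlation the 5% error and 80% power are not assured. For assumed ICCs of 0.1 to 0.3, the planned test's error is about 6.2% to 8.6%, and a valid analysis at 27 per arm has about 75% down to 68% power. The power loss belongs to the corrected analysis; the planned test keeps most of its rejection rate because its error is inflated. These figures rest on the assumed ICC, on pairs formed within arm, and on the article's own difference and SDs.

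**What to change.** - Record a pair identifier for every student and state whether pairs are formed within arm.
- Make the primary analysis a linear mixed model of total training time on arm, with a random pair effect and Satterthwaite or Kenward-Roger degrees of freedom. A t test on pair means is a simpler alternative.
- If 27 per arm leaves a student unpaired, enter that student as a cluster of size one. This settles the variance only; the plan should also say who times and rates that student.
- Account for pairs in the secondary comparisons, where the planned Mann-Whitney and chi-square tests make the same independence assumption.
- Replace the flat 80% with power over an ICC range such as 0.1 to 0.3. If 80% is to be kept, the sizes in Step 6 show what that takes; otherwise state the lower power openly.

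The cost is one extra variable and a change of analysis wording, with no new measurements. The analysis gives up some degrees of freedom (about 1.6 points of power if the ICC is in fact zero), and the stated power becomes less favourable.

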**Fig. 3 Fig3:**
[figure not shown]
Standardized silicone suture pad

Training pairs are required to rate each other throughout the training process until they reach the predefined competency levels for knot quality, suture position, and time. Procedural competency is assessed using a previously validated modified 23-point implementation checklist [14] (Table 1), originally published by Munz et al. [29].

Knot quality is scored using a 5-point scale designed by Muresan et al. [10], which assesses a knot’s throws, tightness, edge opposition, and ability to hold under tension (Table 2). Furthermore, accuracy is recorded by measuring the distance (mm) of the stitch from the edge of the entry and exit points of the standardized suture pad. Operative time is also recorded.

A trainee demonstrates competency for the C-loop upon finishing it in ≤01:15 (min:sec), attaining ≥18 points on the procedural implementation checklist, scoring ≥4 on the knot quality scale, and maintaining stitching ≤2 mm from the edge of the suture pad’s entry and exit points (Table 3). According to the available medical literature, experienced surgeons (expert level) reach these goals for the surgical C-loop [14]. Once a student has reached competency according to his or her training partner, a specially trained peer tutor is asked to provide expert assessment. If the participant then performs a C-loop, attaining the aforementioned competency criteria under supervision of the tutor, he or she is considered proficient in the technique; thus proficiency is achieved once a trainee completes the C-loop suturing technique on two consecutive occasions with the predefined competency criteria – once for the partner and once for the peer tutor assessment.

### Primary endpoint

The primary endpoint is total training time needed to reach proficiency in a predefined standardized suturing and knot tying technique.

### Secondary endpoints

Secondary endpoints include the number of attempts, procedure subscore differences, and knot quality subscore differences.

### Tertiary endpoints

Tertiary endpoints involve subanalyses of gender differences and the influence of video game experience. Surgery has traditionally been a male-dominated field and research has demonstrated that male medical students are faster at acquiring surgical skills and demonstrate superior visuospatial skills in comparison to their female peers [30–33]. We will explore this further by comparing male and female performance in both groups for total time taken and number of attempts. Furthermore, we will explore the influence of video game experience, in years, on total time taken and number of attempts, for both groups.

### Statistical analysis

The empirical distributions of all parameters of interest are described using mean and standard deviation in case of continuous data, with absolute and relative frequencies in case of categorical parameters. Possible difference in the primary outcome, time to reach proficiency, will be tested using a two-sided *t* test. All secondary parameters including subgroup analyses will be descriptively analyzed according to their underlying distribution, two-sided Mann-Whitney *U* tests in case of continuous parameters, and Chi-square test in case of categorical data. Graphical statistical methods will illustrate the findings, whenever appropriate.

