### Randomization

Participants are randomly allocated to either the sequential learning group (group 1) or control group (group 2) in a 1:1 ratio. The randomization of subjects is performed by an employee otherwise not involved in the study using sealed envelopes labeled by block. Trainees are allocated to groups without stratification by gender or gaming experience. Although this study would benefit from a 1:1 ratio of men to women, this cannot be mandated since the data is collected through participation in a university elective course which is offered on a first-come-first-serve basis. Consequentially, we cannot explore outcome differences in heterogeneous or homogeneous groups, e.g., male-female, male-male, female-female, in a standardized manner; there may be an influencing factor that stems from the communication dynamic, previous experience of a partner, etc. We aim to explore these differences by comparing outcomes between pair group subgroup analysis following data acquisition. An employee of the Department of Medical Biometry at Heidelberg University, who is otherwise not involved with the training, tests, or data collection from the present study, assigned block randomization.

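### The primary t test is valid but ignores gender and gaming experience, which were not stratified; prespecified adjustment is a cheap efficiency gain

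*Protocol article*

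**What the plan says.** **Primary analysis.** The endpoint is defined under Primary endpoint: "The primary endpoint is total training time needed to reach proficiency in a predefined standardized suturing and knot tying technique". Under Statistical analysis the test is fixed: "Possible difference in the primary outcome, time to reach proficiency, will be tested using a two-sided" t test. No covariate is named.

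**Allocation.** The Randomization section describes 1:1 allocation "using sealed envelopes labeled by block", and adds: "Trainees are allocated to groups without stratification by gender or gaming experience". It explains that an equal number of men and women cannot be required, because places in the elective course go to students in order of sign-up.

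**Gender and gaming.** The Tertiary endpoints section cites evidence that "male medical students are faster at acquiring surgical skills and demonstrate superior visuospatial skills in comparison to their female peers". On gaming it makes no such claim; it says that "we will explore the influence of video game experience, in years, on total time taken and number of attempts, for both groups". Both factors are used only at this level: "Tertiary endpoints involve subanalyses of gender differences and the influence of video game experience".

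**Sample size.** Sample size determination takes a mean difference of 15 s, SDs of 15.6 s and 22.2 s, two-sided 5% and 80% power, and arrives at 27 per group. No covariate enters.

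**The concern.** The primary endpoint is a time to reach proficiency, and the protocol itself presents gender as related to speed of acquiring surgical skills. It considers gaming experience worth relating to the same outcome. Neither was used in the allocation, and the gender mix is outside the investigators' control. Adjustment in the analysis is then the remaining way to use this information in the arm comparison, and the primary test does not do so. The tertiary subanalyses describe how the two factors relate to time; they do not adjust the difference between arms.

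Two things are at stake in a trial of 54. Variance that the two factors could explain stays in the error term, and power has little slack: 0.805 at 27 per arm and 0.789 at 26. Also, a chance difference in gender mix stays in the estimate. If the investigators adjust for such a difference only after seeing it, the adjustment can be criticized as data-driven.

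**Working it through.** **Inputs.** From Sample size determination: difference 15 s, SDs 15.6 s and 22.2 s, n = 27 per arm, two-sided 5%. Not in the documents, and therefore assumed over a range: R², the share of within-arm variance in training time explained by gender and gaming years together. Also assumed, for the imbalance figures only: 27 of the 54 students are men.

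**Step 1: reproduce the plan's figure.**
- Common SD = √[(15.6² + 22.2²)/2] = √368.1 = 19.19 s.
- SE of the difference = 19.19 × √(2/27) = 5.22 s; noncentrality = 15/5.22 = 2.87.
- Noncentral t, 52 df: power 0.805. At 26 per arm it is 0.789.

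So 27 per group is right for the unadjusted test, and 0.805 is the reference value.

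**Step 2: power after adjusting for two covariates.**
- Residual SD = 19.19 × √(1 − R²).
- Two covariates leave 54 − 4 = 50 df.
- Chance imbalance in the covariates inflates the variance of the adjusted difference by about 1 + 2/(54 − 2 − 2 − 1) = 1 + 2/49 = 1.041.
- SE = residual SD × √1.041 × √(2/27).

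| Assumed R² | Residual SD (s) | SE (s) | Noncentrality | Net power | Power if the inflation is ignored |
|---|---|---|---|---|---|
| 0 | 19.19 | 5.33 | 2.82 | 0.789 | 0.804 |
| 0.05 | 18.70 | 5.19 | 2.89 | 0.809 | 0.824 |
| 0.10 | 18.20 | 5.05 | 2.97 | 0.829 | 0.844 |
| 0.20 | 17.16 | 4.76 | 3.15 | 0.870 | 0.883 |

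The net column is the one to use. It equals the unadjusted 0.805 at R² of about 0.04. The worst case, R² = 0, costs 0.805 − 0.789 = 0.016. The gain is 0.829 − 0.805 = 0.024 at R² = 0.10 and 0.870 − 0.805 = 0.065 at R² = 0.20.

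**Step 3: check by simulation.** 4,000 runs per setting, 27 per arm, unstratified, the two stated SDs, half men, skewed gaming years.

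| R² | Type I error, t test | Type I error, adjusted | Power, t test | Power, adjusted |
|---|---|---|---|---|
| 0 | 0.051 | 0.056 | 0.810 | 0.796 |
| 0.10 | 0.052 | 0.051 | 0.802 | 0.830 |
| 0.25 | 0.053 | 0.050 | 0.791 | 0.886 |

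The simulation error of a type I rate is √(0.05 × 0.95/4000) = 0.003, so both methods are consistent with 5%. The power figures agree with Step 2.

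**Step 4: chance imbalance in gender.** With 27 men among 54 and 27 per arm, k men in one arm gives a gap of |2k − 27|/27. Possible gaps are 3.7, 11.1, 18.5, 25.9 points and upward. A gap above 20 points therefore means at least 25.9 points (17 men against 10), and its hypergeometric probability is 0.102.

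To give a scale: if gender alone explained 10% of the variance (assumption), the difference between men and women would be 2 × √(0.10 × 368.1) = 12.1 s. A gap of 7/27 would move the observed arm difference by 12.1 × 0.259 = 3.1 s, about one fifth of the planned 15 s.

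**The case against.** The strongest case against is that nothing here is wrong. A t test is valid in a randomized trial, it matches the comparison on which the sample size was based, and it reaches its 80% target. Adjustment is optional, its benefit rests on an R² that the documents do not give, and below about 4% it loses power. All of this stands, and it is why the point is one of efficiency only.

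A reader might infer more than the documents support, in three ways:
- *That the t test destroys balance or biases the result.* Balance comes from the allocation. A chance difference between arms does not bias the randomized comparison on average, and the test's error rate already allows for it.
- *That both factors are presented as predictors.* This holds for gender only. For gaming the protocol announces an exploration and asserts no effect.
- *That precision is given away at no cost.* Adjustment uses two degrees of freedom and inflates the variance slightly, so the gain at R² = 0.10 is about 2 points of power and not 4.

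A further objection is that adjusted models may sit in an analysis plan that is not shown. That may be so for a supportive model. The article, however, fixes the primary test, so an adjusted primary analysis would depart from it.

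Pair training is also raised. Pairs are formed after randomization. If both members are in one arm (assumption), the arm contrast rests on pairs. With about 23 df and no within-pair correlation, the Step 2 formula gives 0.77, 0.79, 0.81 and 0.85 at R² of 0, 0.05, 0.10 and 0.20. This cost is real, but it belongs to the handling of pairs: the unadjusted test on about 25 df drops to 0.79 as well. It is a separate question and is not costed here.

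**Conclusion.** The point holds as a modest efficiency improvement, not as an error or contradiction. The primary t test is valid and adequately powered on the plan's own figures, but it leaves out two characteristics that the protocol intends to relate to the same outcome and did not stratify on. The case is stronger for gender than for gaming.

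The size is uncertain because R² is unknown: from a loss of at most about 1.6 points of power to a gain of about 2.4 points at R² = 0.10 and 6.5 points at 0.20. The chance of a gender gap above 20 points is about 10% if half the students are men; adjustment would largely remove the effect of such a gap on the estimate. All power figures take the pilot difference and SDs as stated and treat participants as independent.

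**What to change.** Before outcome data are examined, specify as the primary analysis a linear model of total training time on arm, gender and years of video game experience. Test the adjusted arm difference at two-sided 5%, and report the unadjusted t test as supportive. In a linear model without interaction, both analyses estimate the same mean difference, so the question asked does not change.

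State that gaming years are recorded before training starts; the article does not give the time of collection. Decide on the handling of training pairs separately, with its own cost in degrees of freedom.

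The cost is a change of wording and two degrees of freedom. Both variables are needed for the planned tertiary analyses in any case, so no new data, participants or procedures are required, and the sample size of 27 per group can stay.
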